#### 2.6.3. Tertiary Outcomes (Parents/Guardians)

##### 24-h Movement Behaviors (Self-Reported)

The level of PA and sitting time will be assessed by the International Physical Activity Questionnaire-short form (IPAQ-SF) [62]. The IPAQ-SF will gather information on physical activity (PA) during the previous week in terms of the number of days, duration, and intensity of vigorous-intensity, moderate-intensity, and walking activities that lasted for at least 10 min. It will also inquire about the amount of time spent sitting on the last seven weekdays. The IPAQ-SF score will be computed in Metabolic Equivalent of Task (MET)-minutes per day or week. Parents/guardians will be classified into meeting or not meeting the PA guidelines. Meeting the PA guidelines will be considered when parents/guardians engage in ≥150 moderate-vigorous PA minutes per week or ≥75 vigorous-intensity PA minutes per week. For the sitting time, participants will be questioned about their sitting time separately for weekdays and weekend days. The 24-h movement guidelines offer an explicit guideline about recreational screen time: ≤3 h daily as a subcomponent of the sedentary guideline (i.e., in addition to the less than 8-h sedentary time guideline) [63]. In this project, recreational screen time will be self-reported. Participants will be asked a series of questions during a household interview regarding their sedentary activities during leisure time as follows: (a) “In a typical week in the past three months, how much time did you usually spend on a computer, tablet or iPad including watching videos, playing computer games, emailing or using the Internet?”; (b) “In a typical week in the past three months, how much time did you usually spend playing other types of video games on a game console or hand-held electronic device?”; (c) “In a typical week in the past three months, how much time did you usually spend watching television, DVDs or videos?” Respondents will be provided with a continuous response option. The amount of time spent on each activity involving screens will be added together to obtain an overall estimate of daily recreational screen time. Screen time will be categorized into meeting (vs. not meeting) the guideline. Sleep duration will be self-reported by using the following question for weekdays and weekends independently: “How many hours do you usually spend sleeping in a 24-h period, excluding time spent resting?” Responses will be reported as a continuous variable and rounded to the nearest half-hour by the interviewer. Sleep duration will be categorized as a binary variable to compare parents/guardians meeting age-specific sleep guidelines (i.e., 7–9 h daily for adults aged 18–64 years; 7–8 h daily for adults aged ≥65 years) with those not meeting that guideline [64].

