## Abstract

**Objective:** The aim of this paper is to describe the protocol of pilot cluster randomized controlled trial (RCT) that will evaluate the effects of a lifestyle-based intervention. The *Archena Infancia Saludable* project will have several objectives. The primary objective of this project is to determine the 6-month effects of a lifestyle-based intervention on adherence to 24-h movement behaviors and Mediterranean diet (MedDiet) in schoolchildren. The secondary objective of this project is to test the intervention effects of this lifestyle-based intervention on a relevant set of health-related outcomes (i.e., anthropometric measurements, blood pressure, perceived physical fitness, sleep habits, and academic performance). The tertiary objective is to investigate this intervention’s “halo” effect on parents’/guardians’ 24-h movement behaviors and adherence to the MedDiet. **Methods:** The *Archena Infancia Saludable* trial will be a cluster RCT submitted to the Clinical Trials Registry. The protocol will be developed according to SPIRIT guidelines for RCTs and CONSORT statement extension for cluster RCTs. A total of 153 eligible parents/guardians with schoolchildren aged 6–13 years will be randomized into an intervention group or a control group. This project focuses on two fundamental pillars: 24-h movement behaviors and MedDiet. It will mainly focus on the relationship between parents/guardians and their children. Behavior change strategies for dietary and 24-h movement behaviors in schoolchildren will be based on healthy lifestyle education for parents/guardians through infographics, video recipes, brief video clips, and videos. **Conclusions:** Most of the current knowledge on 24-h movement behaviors and adherence to the MedDiet is based on cross-sectional or longitudinal cohort studies, warranting a need to design and conduct RCTs to obtain more robust evidence on the effect of a healthy lifestyle program to increase 24-h movement behaviors and to improve adherence to the MedDiet in schoolchildren.

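### The parents' PA-guideline rule counts a vigorous minute as one minute in one limb and implicitly as two in the other, so some more active parents are classed below less active ones (minor, tertiary outcome)

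*Protocol article*

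**What the plan says.** The rule stands in section 2.6.3, Tertiary Outcomes (Parents/Guardians), under 24-h Movement Behaviors (Self-Reported). The IPAQ-SF records "the number of days, duration, and intensity of vigorous-intensity, moderate-intensity, and walking activities that lasted for at least 10 min", so moderate and vigorous minutes are available separately. Two outputs are derived from it:

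- A continuous score: "The IPAQ-SF score will be computed in Metabolic Equivalent of Task (MET)-minutes per day or week".
- A binary status: "Parents/guardians will be classified into meeting or not meeting the PA guidelines". The cut-points for meeting are "≥150 moderate-vigorous PA minutes per week or ≥75 vigorous-intensity PA minutes per week".

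The section gives no weight for converting vigorous into moderate minutes and no clause for mixed activity. The binary status does not use the MET-minute score.

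The abstract gives the role of these outcomes: "The tertiary objective is to investigate this intervention’s “halo” effect on parents’/guardians’ 24-h movement behaviors and adherence to the MedDiet".

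**The concern.** A rule that dichotomises activity should not place a more active person below a less active one. This rule can, because its two limbs value a vigorous minute differently. A parent just short of 75 vigorous minutes loses the double credit on all of them and must then reach 150 minutes with every minute counted once.

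What is at stake is the binary PA status used to look for a halo effect in parents. A parent who replaces some moderate activity with vigorous activity can drop from meeting to not meeting although total activity, weighted for intensity, has risen.

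**Working it through.** **Inputs (all from section 2.6.3).** M = moderate minutes per week, V = vigorous minutes per week. Rule as written: meets if M + V ≥ 150 or V ≥ 75. The implied weight is 150/75 = 2 moderate minutes per vigorous minute; this is derived from the cut-points and not stated.

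**Step 1. Apply the rule and compare it with M + 2V ≥ 150.**

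| M | V | M + V | Rule as written | M + 2V | M + 2V ≥ 150 |
|---|---|---|---|---|---|
| 150 | 0 | 150 | meets | 150 | meets |
| 0 | 75 | 75 | meets | 150 | meets |
| 149 | 0 | 149 | does not | 149 | does not |
| 60 | 60 | 120 | does not | 180 | meets |
| 70 | 70 | 140 | does not | 210 | meets |
| 75 | 74 | 149 | does not | 223 | meets |

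The last row is the extreme case: 223/150 = 1.49, or 49% above the threshold.

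**Step 2. Does the reversal depend on the 2:1 weight?** With weight w per vigorous minute, the 70/70 parent scores 70 + 70w and the 0/75 parent scores 75w. The first exceeds the second when 70 > 5w, that is, w < 14. So the reversal holds for any plausible weight; only its size depends on w. The highest score among those not meeting and the lowest among those meeting are:

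| w | Highest, not meeting | Lowest, meeting |
|---|---|---|
| 1 | 149 | 75 |
| 1.5 | 186 | 112.5 |
| 1.75 | 204.5 | 131.25 |
| 2 | 223 | 150 |
| 2.5 | 260 | 150 |

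**Step 3. Who is affected at w = 2?** Those with V < 75, M + V < 150 and M + 2V ≥ 150. At V = 50 this is M from 150 − 100 = 50 up to 99. At V = 70 it is M from 150 − 140 = 10 up to 79.

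**Step 4. Direction of the discrepancy.** If M + V ≥ 150, then M + 2V ≥ 150, since V is not negative. If V ≥ 75, then 2V ≥ 150. So at w = 2 nobody who meets the present rule fails the weighted one. For w below 2 this no longer holds: at w = 1.5, a parent with 75 vigorous minutes alone scores 112.5 and still meets.

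**Step 5. Change within a parent.** Moving from M = 150, V = 0 to M = 70, V = 70 switches the status from meeting to not meeting. The weighted total goes from 150 to 70 + 70w, which is a rise whenever w > 80/70 = 1.14; at w = 2 it is 150 to 210.

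**Step 6. Other reading of the first limb.** If 150 was meant for moderate minutes only, the gap widens: M = 149, V = 74 does not meet, at 149 + 148 = 297 equivalent minutes.

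**The case against.** The rule is complete and reproducible, and nothing else in the article contradicts it. It states no exchange rate, so to call a parent wrongly classed requires a benchmark that the article does not give. That stands in part: 2:1 is an inference, and the exact set of affected parents rests on it. The reversal between the 70/70 and 0/75 parents does not.

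A clause on mixed activity may also have been lost when the full protocol was condensed. But the article prints a rule with numeric cut-points and an explicit alternative, so the point concerns what is stated, not what is left out.

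A reader might infer more than the document supports:

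- *That the error always runs one way and so biases the halo effect.* One-sidedness holds at w = 2 or above, not below (Step 4). The same rule applies to both arms at both visits, so no difference between arms is built in; one would arise only if the intervention moved parents into or out of the affected region.
- *That a real shift to mixed activity would go unseen.* The continuous MET-minute score would still register it, and section 2.5.2 plans a mixed model for each dependent variable.
- *That a composite of the three guidelines is damaged.* For parents, section 2.6.3 defines separate statuses for PA, screen time and sleep, and no composite.
- *That a large share of parents is affected.* The article gives no distribution of their activity, so no share can be derived.

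**Conclusion.** The point holds as a minor defect of definition. The two limbs value a vigorous minute differently, and the rule therefore ranks some more active parents below less active ones. The size per person is bounded: at 2:1, up to 223 equivalent minutes classed as not meeting against a threshold of 150. The number of parents is unknown.

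The consequence is confined to one dichotomised tertiary outcome in parents. The sample size in section 2.5.1 and the children's primary outcomes do not depend on it. The size and the affected region assume the 2:1 weight implied by 150 and 75; the existence of a reversal needs only w < 14.

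**What to change.** In section 2.6.3, define meeting the PA guidelines as moderate minutes + 2 × vigorous minutes ≥ 150 per week, applied at baseline and after the intervention. Add that 2:1 is the weight implied by the protocol's own two cut-points. Both are kept: 150 moderate minutes alone and 75 vigorous minutes alone still just meet, 149 moderate minutes alone still does not, and nobody moves from meeting to not meeting.

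A cut-off on the MET-minute score is not a ready substitute: the article gives no MET weights and does not say whether walking, which the IPAQ-SF records separately, would count towards it. The new sentence should leave the treatment of walking as it is intended under the present rule.

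The cost is one sentence and one line of code. No new data are needed.

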
##### Adherence to the Mediterranean Diet

To assess adherence to the MedDiet, parents/guardians will also be administered the 17-item energy-restricted Mediterranean Adherence Screener (er-MEDAS) [64], used in the PREDIMED (*PREvención con DIeta MEDiterránea*)-Plus trial [65]. The er-MEDAS was developed using the 14-item MEDAS [66], which had been previously validated. Each of the 17 items that pertain to typical dietary habits will be evaluated and assigned a score of either zero or one point. Therefore, the global score will range from zero to 17 points, with zero points denoting no adherence to the MedDiet and 17 indicating maximum adherence to the MedDiet [65].

#### 2.6.4. Covariates

Age and sex will be self-reported by schoolchildren and parents/guardians, respectively. Parents/guardians will be asked for country birth (of their children and themselves) and their marital status. The somatic maturity of schoolchildren will be estimated according to the prediction models proposed by Moore et al. [67]. The socioeconomic status (SES) of the participants will be evaluated using the Family Affluence Scale (FAS-III) [68], which will be answered by the parents or guardians. The FAS-III comprises six items related to household possessions such as vehicles, computers, bathrooms, dishwashers, and family travel. The score will be calculated by summing up the responses, ranging from 0 to 13 points. The final score will determine the participants’ SES category as low (0–2 points), medium (3–5 points), or high (≥6 points). Information about the educational level of parents/guardians will be requested. Possible options will be (a) incomplete primary education, (b) complete primary education, (c) incomplete secondary education, (d) complete secondary education, (e) incomplete higher education, or (f) complete higher education. The body weight and body height of the parents/guardians will be self-reported. Body mass index (BMI) will be computed by dividing body weight (in kg) by height (in squared meters). Subsequently, BMI status will be established by the WHO criteria [69] as follows: underweight <18.5, normal weight 18.5–24.99, overweight 25–29.99, or obesity ≥30. Parents’/guardians’ perception of their child’s body mass index status will be evaluated with the following question: “In relation to his/her height, which of the following options best describes your child’s body weight?: (1) substantially above normal, (2) slightly above normal, (3) normal, (4) below normal” [70]. This same question will be done four their perception of their own body mass index status as follows: “According to your height, which of the next options best describes your body weight: (1) substantially above normal, (2) slightly above normal, (3) normal, (4) below normal?” [70].

### 2.7. Ethical Considerations and Dissemination

The *Archena Infancia Saludable* project has been previously registered in (ClinicalTrials.gov ID NCT05620303) and has been approved by the Ethics Committee of the Albacete University Hospital Complex and the Albacete Integrated Care Management (ID 2202–132). Similarly, this trial will be performed in accordance with the Helsinki Declaration and respecting the human rights of the participants involved.

All study participants will receive written informed consent. All participants will be informed that they have the right to withdraw from the study at any point without giving reason. The results of this project will be disseminated to academic audiences by presentations at national and international conferences and through peer-reviewed publications in relevant journals. The results will be disseminated to the general population, academic audiences, and policy makers and through seminars, social networks, and press releases.

## 3. Discussion

The *Archena Infancia Saludable* project will verify, for the first time, whether a cluster RCT based on 24-h behaviors and adherence to the MedDiet aimed at parents produces improvements in these healthy behaviors among their children. In childhood, unhealthy lifestyle behaviors (e.g., physical inactivity, excessive sedentary time, short sleep duration, unhealthy diet) share several factors in common [71]. They are (1) cumulative; (2) associated with poorer health in adulthood and increased risk of chronic diseases; (3) preventable and a consequence of not carrying out daily health-promoting activities; and (4) influenced by parenting confidence and skills. Despite this, it has been found that most parents/guardians have positive intentions to support their children’s health behaviors, and yet many are unable to promulgate this support [72]. Therefore, parents need innovative and attractive strategies that are not time-consuming and are adapted to the stressful pace of life today.

Implementing healthy lifestyle habits during childhood is a crucial opportunity for primordial prevention [73,74]. In regard to behavioral interventions, schools provide an ideal setting for effective knowledge transfer and education [75,76]. Additionally, involving families in the intervention can create a supportive environment at home and potentially enhance the impact of the intervention [77]. In general, interventions have tended to focus on health education and the provision of guidelines or recommendations with limited or no training of parents and little recognition of the importance of the role of parents in developing healthy lifestyle habits [71]. In this sense, the *Archena Infancia Saludable* program will seek to provide parents/guardians with numerous practical resources based on 24-h movement behaviors and MedDiet that can be applicable and feasible for their children on a daily basis and adjusted to their real context, beyond theoretical concepts and contents.

Guidelines or recommendations from institutions and scientific experts strongly encourage a MedDiet as a healthy eating pattern that could diminish the risk of chronic noncommunicable diseases since childhood [38,39]. This fact is also consistent with the recommendation of meeting with 24-h movement guidelines [1,2], since the current evidence suggests that these guidelines may have essential implications for health and are linked with several desirable health outcomes in young [65] and adult populations [6,7]. Based on the low levels of the young population meeting the 24-h movement guidelines as well as low adherence to the MedDiet (especially in this region of Spain [45]), it is clear that knowledge, awareness, and implementation of these healthy behaviors by the general population need to be improved in combination with one another for their potential synergistic effect [4,10,28,78].

On the other hand, the United Nations and the WHO have established nine international objectives for noncommunicable diseases to achieve by 2025 [79]. Correspondingly, the target of Sustainable Development Goal 3.4 is to decrease the number of deaths caused by noncommunicable diseases by one-third and support well-being and mental health by 2030 [80]. Unhealthy eating habits and insufficient physical activity are among the primary factors causing disability and a considerable number of chronic noncommunicable diseases worldwide [12,81,82]. Providing intervention programs based on scientific evidence (such as the *Archena Infancia Saludable* program) to improve dietary patterns and lifestyles seems necessary, as it could play an important role in public health.

Additionally, it is worth mentioning that in this cluster RCT of the *Archena Infancia Saludable* project, only one school will be selected. This decision is based mainly on the intention to carry out this intervention program as a pilot test to obtain a more consolidated and effective version of the *Archena Infancia Saludable* program. For this purpose, we will try to obtain feedback from parents/guardians and teachers on the functioning of the project, such as suggestions for improvement and barriers to adherence to the intervention program. We will also try to seek additional sources of funding to increase the resources and methodological quality of this cluster RCT, including all the knowledge acquired in this pilot study, all other schools in the municipality, as well as a larger sample of participants. The ultimate goal of this project is to consolidate the intervention program to be implemented on a scaled basis in all schools in the municipality in future editions, as is being done in projects carried out in secondary schools in Archena that include a larger sample [44].

## 4. Conclusions

Most of the current knowledge on 24-h movement behaviors and adherence to the MedDiet has been based on cross-sectional or longitudinal cohort studies, which warrants further evidence by conducting well-designed RCTs to assess the effect of a healthy lifestyle program on adherence to 24-h movement behaviors and the MedDiet in schoolchildren.

## Figures and Tables

**Figure 1 children-10-00738-f001:**
[figure not shown]
The *Archena Infancia Saludable* project.

**Figure 2 children-10-00738-f002:**
[figure not shown]
Examples of infographics used in the *Archena Infancia Saludable* project.

**Table 1 children-10-00738-t001:** Summary of the variables examined in the *Archena Infancia Saludable* project.

Variables	Schoolchildren Variables		Parents or Guardians Variables	
	Measurement	Tool	Measurement	Tool
Age	- Self-reported.	- Ad hoc questionnaire.	- Self-reported.	- Ad hoc questionnaire.
Sex	- Self-reported.	- Ad hoc questionnaire.	- Self-reported.	- Ad hoc questionnaire.
Socioeconomic status	- Objective.	- FAS-III.		
Educational level			- Self-reported.	- Ad hoc questionnaire.
Immigrant status	- Objective.	- Ad hoc questionnaire.		
Marital status			- Self-reported.	- Ad hoc questionnaire.
Perception of their child’s BMI status			- Self-reported.	- Ad hoc questionnaire.
Perception of their own BMI status			- Self-reported.	- Ad hoc questionnaire.
Active transportation	- Self-reported.	- PACO questionnaire.		
Resting blood pressure and heart rate	- Objective.	- Omrom^®^ EVOLV HEM-7600T-E.		
Sleep-related problems	- Proxy-reported.	- BEARS scale.		
Health-related quality of life	- Self-reported.	- CHU9D.		
Self-reported physical fitness	- Self-reported.	- IFIS scale.		
Academic performance	- Objective.	- School records.		
Anthropometric measures	- Objective.	- Tanita BC-545, Leicester Tanita HR 001. - Constant tension tape.	- Self-reported.	-Ad hoc questionnaire.
Physical activity	- Objective. - Self-reported.	- Actigraph GT3x. - YAP-S.	- Self-reported.	- IPAQ-short form.
Sedentary behaviors	- Objective. - Self-reported.	- Actigraph GT3x. - YAP-S.	- Self-reported.	- IPAQ-short form.
Recreational screen time	- Proxy-reported.	- Ad hoc questionnaire.	- Self-reported.	- IPAQ-short form.
Sleep duration	- Objective. - Proxy-reported	- Actigraph GT3x. - Ad hoc questionnaire.	- Self-reported.	- Ad hoc questionnaire.
*Siesta*	- Objective.	- Ad hoc questionnaire.		
Adherence to the MedDiet	- Self-reported.	- KIDMED.	- Self-reported.	- PREDIMED questionnaire.

BEARS, Bedtime Issues, Excessive Daytime Sleepiness, Night Awakenings, Regularity and Duration of Sleep, Snoring; BMI, body mass index; CHU9D, Child Health Utility 9D; FAS-III, Family Affluence Scale-III; IFIS, International Fitness Scale; IPAQ, International Physical Activity Questionnaire; KIDMED, Mediterranean Diet Quality Index for Children and Teenagers; MedDiet, Mediterranean diet; PACO, *Pedalea y Anda al Cole*; PREDIMED, PREvención con DIeta MEDiterránea; YAP-S; Youth Activity Profile—Spain.

## Data Availability

Not applicable.
